## Abstract

**Background:**

Exacerbations of chronic obstructive pulmonary disease (COPD) are one of the main causes of mortality, and early detection of exacerbations is thus essential. Telemedicine solutions have shown promising results for the detection of exacerbations in COPD and have increasingly been used. However, the effect of telemedicine is divergent. According to several studies, respiration rate (RR) increases before, during, and after an exacerbation and the change is measurable with several contactless devices. Despite this, RR is rarely measured, and telemedicine solutions only use wearable devices for measuring RR, even though wearable respiratory monitoring devices have been associated with certain drawbacks. Contactless devices are often used during sleep, as measurements conducted during sleep minimize the risk of disturbance from physical activities. However, the potential of measuring RR and heart rate (HR) during sleep for the detection of exacerbations in COPD remains unclear.

**Objective:**

The aim of this observational study is to investigate whether contactless measurement of RR, HR, and sleep stages can be used to detect exacerbations in people with COPD.

**Methods:**

An observational study including 50 participants with COPD will be conducted. The participants reside in Aalborg municipality, located in the North Denmark Region. Participants will use a contactless monitor (Sleepiz One+) near their bed during sleep for a period of 4 months. After data collection, descriptive statistics will be used to identify any extremes or variations in RR, HR, or sleep stages in the nights preceding an exacerbation. Correlation analysis will be performed to evaluate the relationship between the number of exacerbations and extremes or variations in RR, HR, or sleep stages. Finally, qualitative interviews will be conducted with 12 participants to explore their experiences of sleeping with the monitor nearby.

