### Study Setting

After the participants have received and completed the questionnaires and consent forms, a researcher from AAU will collect the documents at the participants' homes. Subsequently, a contactless radar-based monitor (Sleepiz One+) will be placed near the participants’ bed. The monitor measures RR, HR, and sleep stages, including rapid-eye-movement sleep, light sleep, and deep sleep. The participants are asked to take measurements throughout the study period. The monitor measures changes in distance originating from breathing activity and heart contractions by using Doppler radar. These distance changes are analyzed using signal processing algorithms to extract RR and HR every fifth second.

The monitor is positioned on a stand 5-10 cm above mattress level, 40-50 cm from the participant pointing to the lower part of the chest. The monitor measures the participant during sleep and only measures the person who is positioned closest to the monitor. Therefore, the participants will be instructed to stay closest to the monitor during sleep, since it would disrupt the measurements if partners were sleeping closest to the monitor. Furthermore, participants will be instructed to turn on the monitor before going to sleep and turn it off upon waking throughout the entire study to ensure consistent data collection. This approach also prevents the monitor from recording data from partners who may go to bed earlier or stay in bed longer than the participants.

Neither the nurses nor the participants will have access to the data from the monitor during the study. Data from the monitor are solely used retrospectively to investigate whether it is possible to identify changes in RR, HR, or sleep stages preceding exacerbations. After the researcher from AAU had placed the monitor at the right position and ensured that the monitor works, data collection was carried out for 4 months.

The data will automatically be transmitted through Wi-Fi to a web application connected to the monitor, enabling data extraction. This web application allows users to view and analyze data collected by the contactless monitor. Participants will be registered as users in the web system by a researcher from AAU, who will also connect a monitor to each individual participant.

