### Statistical Analysis

Overall, the data analysis will include descriptive statistics and logistic regression. Descriptive statistics will be used to calculate mean, SD, and variance for RR, HR, and the time spent in different sleep stages. Logistic regression is particularly relevant when working with binary outcomes to calculate the probability of an event occurring based on one or more independent variables. Since this study investigates whether changes in physiological parameters occur in the nights preceding an exacerbation, logistic regression is an appropriate method for analysis. Logistic regression will be used to calculate the probability of developing an exacerbation based on the descriptives derived from RR, HR, and sleep stages as independent variables. Odds ratios based on logistic regression and the *F* statistic (*P*<.05) will determine whether each descriptive is independently associated with developing an exacerbation. Furthermore, correlations between the descriptives will be examined.

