## Discussion

### Anticipated Findings

The main finding of this study is presumed to be a new way to detect COPD exacerbations using contactless sleep monitoring. The study aims to provide knowledge regarding the possibility of detecting COPD exacerbations through frequent measurements of RR, HR, and sleep stages collected by using a contactless monitor during sleep. If the study proves that exacerbations can be detected by contactless measurements, the results have the potential to improve the ability to predict exacerbations in the future. Predicting exacerbations enables the possibility of initiating early treatment, which is expected to reduce hospitalizations and increase the quality of life among people with COPD.

Additionally, the study is also expected to provide knowledge regarding the experience of using the monitor more permanently. This is considered valuable knowledge about the potential of the monitor, as users’ experience and acceptance are important to consider when developing and implementing new technologies [46,47].

An expected strength of this study is the high frequency of measurements conducted over an extended time period. To our knowledge, no previous studies have monitored RR by a contactless monitor with a high frequency of measurements over an extended time period in people with COPD. However, continuous data collection can be crucial in this study because missing data from the nights preceding an exacerbation can reduce the ability to detect exacerbations, as symptoms primarily change a few days prior to onset [48]. While the recommendation to turn the monitor on/off throughout the entire project period is expected to meet the participants’ needs regarding privacy in the bedroom, this recommendation can also increase the risk of missing data. Therefore, it is important to be aware of missing data throughout the study period.

Another expected strength is that the measurements are conducted during sleep without physically touching the participants. This is expected to eliminate the discomfort associated with wearable equipment. Moreover, conducting measurements during sleep reduces the risk of data being influenced by factors like physical activity, which can be challenging to control when people perform the measurements at home during the day on their own. Øverst på formularen

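### Exacerbation probabilities fitted and read in one cohort can look like detection even when the monitor signals carry no information

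*Protocol article*

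**What the plan says.** The abstract (Methods) describes a first step, taken once all monitor data are in: "descriptive statistics will be used to identify any extremes or variations in RR, HR, or sleep stages in the nights preceding an exacerbation". Its next sentence reads: "Correlation analysis will be performed to evaluate the relationship between the number of exacerbations and extremes or variations in RR, HR, or sleep stages".

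The Statistical Analysis section describes the model: "Logistic regression will be used to calculate the probability of developing an exacerbation based on the descriptives derived from RR, HR, and sleep stages". It names the inputs: "Descriptive statistics will be used to calculate mean, SD, and variance for RR, HR, and the time spent in different sleep stages". Study Setting lists the stages as "including rapid-eye-movement sleep, light sleep, and deep sleep". Each term is then judged by a threshold: "Odds ratios based on logistic regression and the *F* statistic (*P*<.05) will determine whether each descriptive is independently associated".

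There is one cohort: 50 recruited, 40 assumed for power (Sample Size). The Discussion (Anticipated Findings) presumes that the main finding will be a new way of detecting exacerbations, and begins its statement of consequences with "If the study proves that exacerbations can be detected by contactless measurements". The abstract's Conclusions are more cautious and say only that the findings may clarify whether detection is possible.

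**The concern.** A logistic model fitted to few events and many descriptives adapts to chance patterns in the people who supplied the data. Its probabilities then separate those people well, whether or not the descriptives carry information. The same model applied to the next participant may do no better than a coin toss.

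The article states a fit, a set of probabilities and a P<.05 reading, all in one cohort, and then speaks of proving detection. The open search of pre-exacerbation nights adds a further way for chance patterns to enter. The Discussion itself warns that too few exacerbations may be observed, and that is where this optimism is greatest. What is at stake is the headline conclusion: the study could report a detection signal that does not exist.

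**Working it through.** **1. The plan's own figure.** For one correlation of 0.5, two-sided alpha 0.05 (sidedness assumed) and 90% power:

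n = ((1.960 + 1.282) / atanh(0.5))² + 3 = (3.242 / 0.549)² + 3 = 37.8, so 38.

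Power at n = 40 is 0.916. The stated 40 is reproduced to within 2 participants. It covers a single correlation and says nothing about a multivariable model.

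**2. Candidate descriptives.** RR, HR and three sleep stages make 5 signals. Three summaries each give 5 × 3 = 15. SD and variance of one signal are nearly redundant, so 5 × 2 = 10 is a fair lower reading. Five is included as a lean case.

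**3. Events.** The article gives no expected number. Assumed: 6, 10 or 15 of 40 participants with an event. With 15 descriptives that is 6/15 = 0.4, 10/15 = 0.67 and 15/15 = 1 event per descriptive.

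**4. Participant-level model under pure noise.** 40 rows, independent noise descriptives, ordinary logistic fit; median AUC on the fitted data:

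| Descriptives | 6 events | 10 events | 15 events |
|---|---|---|---|
| 5 | 0.76 | 0.73 | 0.71 |
| 10 | 0.90 | 0.85 | 0.80 |
| 15 | 1.00 | 0.93 | 0.89 |

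On fresh data every cell is about 0.50. Repeat runs with other seeds and settings moved the cells by a few hundredths (for example 0.88 instead of 0.93); the whole range was 0.68 to 1.00.

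**5. Night- or window-level model under pure noise.** The row of the model is not stated, so this layout was also tried: 400 independent rows (assumed), 15 candidates; mean apparent AUC:

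| Kept in model | 10 events | 20 | 30 | 40 |
|---|---|---|---|---|
| Best 1 | 0.68 | 0.63 | 0.61 | 0.60 |
| Best 3 | 0.75 | 0.69 | 0.65 | 0.64 |
| All 15 | 0.82 | 0.74 | 0.70 | 0.68 |

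On fresh data: 0.49 to 0.51. The last row involves no selection, so the optimism does not depend on picking signals.

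**6. P<.05 for each descriptive.** With k independent noise tests, the chance of at least one P<.05 is 1 − 0.95^k: 23% for 5, 40% for 10, 54% for 15. Simulated separate correlations at n = 40 with pairwise correlation 0.5 among 15 descriptives gave 36%.

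**7. The correlation with the number of exacerbations.** Null simulations picked the signal that stood out most before events, then correlated its participant-level value with the count.
- Picked by comparing pre-event nights with everyone's other nights (pooled): P<.05 in about 20 to 38%.
- Picked by comparing with the participant's own other nights: 3 to 7%, that is, nominal.

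The inflation comes from stable differences between people and vanishes with a within-person comparison.

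**8. Choice of validation.** Under no signal, AUC from pooled leave-one-participant-out scores was 0.39 to 0.48, which is biased below 0.50. Outcome-stratified 5-fold AUC averaged within folds was 0.48 to 0.53. A left-out value in the low 0.40s is therefore an artefact of pooling and not the no-signal value.

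**The case against.** The strongest reply is that the article describes no select-then-test procedure. The Statistical Analysis section names its descriptives without reference to exacerbation dates, and nowhere does the text say that only signals found in the search are tested. This stands. A reader might infer from the abstract that a signal is picked from pre-exacerbation nights and then tested on the same people, so that the correlation's P value is invalid. The documents do not support that: the selection step is not stated, and the article's language of changes before an exacerbation fits a within-person comparison, for which the error rate stays nominal.

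Second, the plan names no AUC, threshold or prediction rule; it reports odds ratios and P values. That is correct, and AUC is used here only as a yardstick for how well fitted probabilities separate. But the plan does compute exacerbation probabilities, and the Discussion draws a detection claim from the study, so the yardstick is relevant.

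Third, validation may sit in an analysis plan that is not shown. Silence on it would be no finding. The point is the stated method: fit, probabilities and significance in one cohort, tied to a claim of detection.

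Fourth, the claim is conditional and the Conclusions are cautious. This lowers the weight of the point but leaves the two sections out of step.

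**Conclusion.** The point holds for the logistic model and the detection claim. Probabilities and P<.05 associations obtained in the fitting cohort cannot show that exacerbations are detectable: with 40 participants and no signal, the median apparent AUC is about 0.7 to 1.0 against 0.50 on fresh data. The size rests on assumed events (6 to 15 of 40 participants), 5 to 15 descriptives and independent noise. More events or fewer descriptives shrink it, but the direction does not change.

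It does not hold for the correlation test as written. That test is inflated only if a signal is first picked from pooled pre-event nights, which the article does not say.

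The plan should be changed here. Data collection is unaffected, but the main conclusion depends on it.

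**What to change.** In the abstract's Methods and in Statistical Analysis:

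1. Define an extreme relative to the participant's own baseline, and fix the definition before exacerbation dates from TCN and the registry are merged with monitor data.
2. Fit a penalised logistic model (ridge or Firth).
3. Put the fit and any selection of descriptives inside an internal validation with the participant as the unit. Use bootstrap optimism correction, or repeated, outcome-stratified participant-level k-fold with AUC computed within folds. Do not use pooled leave-one-out AUC, which could hide a real signal.
4. Base any statement on detection on the validated figures. Label the in-sample search and the P<.05 associations as exploratory, and bring Anticipated Findings into line with the abstract's Conclusions.

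This needs no new participants, visits or measurements. The article reports 12 of 50 participants recruited, so there was still time to fix the definition before the data are merged. The cost is a little more analysis work and reported performance less favourable than the in-sample figures. With few events the validated figure will also be imprecise (6 events over 5 folds leave one or two per fold), so its uncertainty should be shown.

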**Results:**

Recruitment started at the end of April 2024. A total of 12 participants have been recruited, and the remaining participants are expected to be recruited during March and April 2025. Six out of 12 participants have completed the data collection and qualitative interview stages. Overall data collection is expected to be completed by September 2025. The results are expected to provide insight into the potential for identifying extremes or variations in RR, HR, or sleep stages in the days preceding an exacerbation. Additionally, the results are expected to assess the correlation between the number of exacerbations and extremes or variations in RR, HR, and sleep stages.

**Conclusions:**

The findings from this study may clarify the possibility of using a contactless monitor to detect exacerbations in COPD. Furthermore, the results may have the potential to improve the ability to predict exacerbations in the future.

**International Registered Report Identifier (IRRID):**

DERR1-10.2196/63230

## Introduction

Chronic obstructive pulmonary disease (COPD) poses a global health challenge. In 2019, around 212 million people were diagnosed with COPD, and it was the third leading cause of death with approximately 3.3 million deaths [1,2]. COPD is associated with significant economic costs, which increase with the progression of the disease [1]. In the European Union, the direct expenses related to respiratory diseases are estimated to comprise approximately 6% of the total annual health care expenditures, with COPD accounting for 56% of respiratory disease expenditures [1].

Exacerbations in COPD are characterized by exacerbation of shortness of breath and/or coughing with increased sputum over a period of <14 days. These escalating symptoms may be accompanied by rapid breathing and/or rapid pulse [1,3]. Frequent exacerbations are associated with reduced quality of life (QoL), increased risk of rehospitalization, and higher mortality rates compared to fewer exacerbations [4]. Hence, it is essential to prevent exacerbations.

Timely treatment of exacerbation reduces the risk of hospitalization and increases QoL [5,6]. Identification of the first symptoms of exacerbations is therefore essential to initiate early treatment. For early detection of exacerbations, telemedicine solutions are increasingly used, which seem to have a positive effect on QoL and hospital admissions [7,8]. However, the effectiveness of telemedicine solutions in preventing exacerbations is not convincing, and the results are generally divergent, indicating the need for further research [7-11].

In telemedicine, monitoring of physiological parameters is widely used for early detection of exacerbations. Primarily, oxygen saturation and heart rate (HR) are measured and used for detection of exacerbations [11-14]. However, the telemedicine solutions are generally based on studies with a low methodological quality, highlighting the need for robust, well-designed clinical trials [14].

According to several studies, both respiration rate (RR) and HR increase before, during, and after an exacerbation [15-17]. Despite measurement of RR being more effective than HR for early detection of exacerbation, only a few telemedicine solutions include measurements of RR [11-14]. The lack of RR measurement may possibly be attributed to the general challenge of measuring RR over an extended time period at home [18]. Moreover, respiratory monitoring equipment has been associated with certain drawbacks such as discomfort and difficulty in use [19]. Overall, the usability of respiratory monitoring systems is sparsely investigated [18].

Various contactless devices are capable of measuring RR [20], including contactless radar-based monitors [21,22]. Existing telemedicine solutions only use wearable devices for RR measurements [19,23-25], even though it seems possible to measure a change in RR during exacerbation using contactless devices [26]. Contactless devices enable free movement and eliminate the discomfort associated with wearable devices. Discomfort can hinder measurement over an extended time period [22,27,28], and contactless devices are therefore increasingly used for measurements of physiological parameters [29]. However, contactless devices require the user to be near the device and are therefore often used for overnight measurements, where the user remains close to the device for an extended time period [20]. During sleep measurement, it is essential that the equipment is contactless to minimize the impact on sleep quality [30]. Sleep monitoring minimizes the risk of measurements being influenced by factors such as physical activity. Several contactless devices are capable of measuring both RR and HR [20-22]. To the best of our knowledge, no previous studies have conducted frequent contactless measurement of RR and HR during sleep for detecting exacerbations in people with COPD.

The overall objective of the study is to investigate whether physiological variables such as RR, HR, and sleep stages can be used to detect exacerbations in people with COPD. This study is based on the hypothesis that data from frequent measurement of RR and HR during sleep can be used to detect exacerbations in COPD. Ultimately, these data may improve the prediction of exacerbations in COPD.

## Methods

### Study Design

This study is a longitudinal observational study and is expected to run from April 2024 to September 2025 [31,32]. This study will recruit participants from the Danish telemedicine service, TeleCare Nord (TCN), which is part of routine care in the North Denmark Region [33]. The telemedicine service includes measurements of oxygen saturation, pulse, blood pressure, weight, and patient-reported outcomes once a week [34].

### Eligibility Criteria

#### Inclusion Criteria

People aged ≥18 years with a diagnosis of COPD will be included in the study, and both men and women are qualified. Moreover, people residing in the Aalborg Municipality will be deemed eligible to participate.

#### Exclusion Criteria

The exclusion criteria are the inability to complete questionnaires, pregnancy, nursing, electronic implants, and children or pets sleeping in the same bed as the participants, as it can disturb the measurements.

### Recruitment

For the observational study, 50 participants will be recruited from Northern Jutland, Denmark. Initially, recruitment is conducted by specialized COPD community nurses (or a related clinician; Figure 1). The specialized COPD nurse gives a short introduction to the trial and in case of someone is interested in participating, a researcher from Aalborg University (AAU) will send a participant information letter by mail. Hereafter, the participants are contacted by a researcher from AAU who will provide further information about the study. If the individual is interested in participating, a consent form and questionnaires regarding baseline information will be sent by mail.

**Figure 1 figure1:**
[figure not shown]
The study procedure from recruitment until the end of the study. AAU: Aalborg University; COPD: chronic obstructive pulmonary disease.

### Study Setting

After the participants have received and completed the questionnaires and consent forms, a researcher from AAU will collect the documents at the participants' homes. Subsequently, a contactless radar-based monitor (Sleepiz One+) will be placed near the participants’ bed. The monitor measures RR, HR, and sleep stages, including rapid-eye-movement sleep, light sleep, and deep sleep. The participants are asked to take measurements throughout the study period. The monitor measures changes in distance originating from breathing activity and heart contractions by using Doppler radar. These distance changes are analyzed using signal processing algorithms to extract RR and HR every fifth second.

The monitor is positioned on a stand 5-10 cm above mattress level, 40-50 cm from the participant pointing to the lower part of the chest. The monitor measures the participant during sleep and only measures the person who is positioned closest to the monitor. Therefore, the participants will be instructed to stay closest to the monitor during sleep, since it would disrupt the measurements if partners were sleeping closest to the monitor. Furthermore, participants will be instructed to turn on the monitor before going to sleep and turn it off upon waking throughout the entire study to ensure consistent data collection. This approach also prevents the monitor from recording data from partners who may go to bed earlier or stay in bed longer than the participants.

Neither the nurses nor the participants will have access to the data from the monitor during the study. Data from the monitor are solely used retrospectively to investigate whether it is possible to identify changes in RR, HR, or sleep stages preceding exacerbations. After the researcher from AAU had placed the monitor at the right position and ensured that the monitor works, data collection was carried out for 4 months.

The data will automatically be transmitted through Wi-Fi to a web application connected to the monitor, enabling data extraction. This web application allows users to view and analyze data collected by the contactless monitor. Participants will be registered as users in the web system by a researcher from AAU, who will also connect a monitor to each individual participant.

The questionnaires will be used to explore health status and health literacy. The health status involves baseline information (gender, age, civil status, educational level, deployment, years since COPD diagnosis, smoking status, and comorbidities), the COPD Assessment Test (CAT) [35], the Medical Research Council (MRC) dyspnea score [36], and The European Health Literacy Survey Questionnaire (HLS-EU-Q16) [37,38]. Additionally, the Danish Short Test of Functional Health Literacy in Adults (DS-TOFHLA) [39] questionnaire will be distributed to assess health literacy.

In cases of missing data for more than 2 consecutive nights, the participants will be contacted by a researcher from AAU by telephone to clarify the underlying reason and resolve that. Once data collection for 4 months (±10 nights) is completed, the monitor is collected by a researcher from AAU.

Data will be extracted from the web application connected to the monitor, TCN, and the National Patient Registry to determine the number and dates of exacerbations. Exacerbations are defined as hospitalizations caused by COPD or self-initiated treatment with antibiotics and/or steroids [40]. To obtain the exact dates of exacerbations, hospitalizations related to COPD will be extracted from the National Patient Registry. Similarly, to determine the dates of exacerbations related to self-initiated treatment, participants are already registering their use of antibiotics and steroids as part of TCN. If self-initiated treatment is registered, a researcher from AAU will contact the COPD nurse to obtain information about when the treatment began, thereby obtaining the exact date of the exacerbation.

